#### Emergency-referral intervention component

Despite ongoing programs, remaining weaknesses were identified in the district referral systems, thus, the project is supporting the development and implementation of locally designed strategies to strengthen district referral systems based on contextual evidence and the requisites for referral systems proposed by Murray and Pearson [29].

Because a whole systems approach was required, the referral intervention is being implemented at the district level. The design takes into account the required layers of coordination starting with prompt decision making at the household level; timely referrals from communities; appropriate triaging and pre-referral care; rapid transportation; and responsiveness at receiving facilities [43,44]. The project activities aim at improving the functioning of the system to respond to all emergency health conditions, with emphasis on obstetric, newborn, and child complications. These activities are linked to and draw upon the presence of the CHA to inform families about early warning signs of complications and facilitate early referrals, as well as to mobilize the development of community-based emergency mechanisms.

The intervention was informed by a mixed-methods formative research study conducted in the three districts. The research found that each district had planned and implemented some strategies and activities but none met the requisites of a strong referral system [29]. Furthermore, the responsibility for referral transport was typically borne by the woman and her family, resulting in delays and catastrophic expenditures. The formative research findings were used to inform the development of district-specific plans. These plans were developed through participatory action research and planning exercises that engaged stakeholders at district and community levels.

Strategies will be implemented by the districts with local resources as well as Connect financial and technical support. Funds mobilized by the districts will support advocacy with local politicians, upgrading health centers to provide emergency care, establishing hospital-based emergency teams, and including emergency care in supervision visits. Components supported by the project include improvements in ambulance transportation; establishment of an emergency telemedicine support, and advance communication system using mobile phones; clinical improvements in staff skills and patient flow for triage and pre-referral care; community mobilization mechanisms initiated and facilitated by CHA; and introduction of standardized emergency-referral forms.

### Evaluation design

The evaluation of the added value of the CHA is designed as a community-based cluster-randomized trial set in three HDSS villages to measure reductions in child mortality and outcomes related to reproductive, maternal, newborn, and child health. Table 3 presents examples of key outcomes of interest [45,46]. The district-wide emergency referral evaluation relies on facility and systems-based data. A plan of implementation research will complement this data, as well as an economic evaluation to assess the overall costs of the program.

**Table 3 T3:** Examples of project maternal, newborn and child health outcomes of interest

Category	Indicator
**Mortality rates (by gender of child)**	• Neonatal mortality rate • Infant mortality rate • Under-age five cumulative mortality rate (q_5_ ) • Estimated under age 5 cause specific mortality rate for malaria, acute respiratory infections,

**Maternal Health Behavior (last live birth)**	• Percent of women who made their first ANC visit before the fourth month • Percent pregnant women who attended four or more antenatal care visits • Percent pregnant women who attended postnatal care visit • Percent women who deliver in a health facility • Proportion of c-sections among last born

**Newborn Health**	• Percent of newborns attending postnatal care visits • Percent of newborns breastfed within 1 hour of birth • Percent of women that report having practiced at least three ENC behaviors

**Under-5 child health**	• Percent episodes of diarrhea in children under 5 treated with ORS + zinc • Percent episodes of cough/pneumonia in children under age five treated with antibiotics • Percent of febrile malaria episodes among children under 5 treated within 24 hours of onset

**Family planning and fertility**	• Contraceptive prevalence rate • Unmet need for family planning • Age specific and total fertility rates

#### Ethical considerations

Ethical approval has been received from the institutional review boards of the IHI, the Tanzanian National Institute of Medical Research, the Tanzania Commission for Science and Technology, and Columbia University. Permission to conduct the intervention and corresponding research was obtained from relevant district and village government authorities. The trial has been registered with the International Standard Randomized Controlled Trial Register (#ISRCTN96819844). In addition, all reporting will follow CONSORT guidelines for cluster-randomized trials [47].

#### Evaluation of the CHA intervention

Villages were randomly assigned to either CHA intervention or comparison within four strata defined by village population size. This ensured that large and small villages would be equally represented in the intervention and control arms of the study. Village boundaries were identified from official government records. Intervention and comparison areas were tested for comparability in baseline mortality and key MNCH behavioral indicators. Analyses confirmed that the sample is balanced, with statistically insignificant differences between the two study arms for each metric tested.

A possible limitation of the design is the potential for clientele of comparison communities to seek care from CHA who are based in nearby treatment communities. To address this possible bias, research modules have been developed to assess comparison-area client exposure to CHA services. This information will permit statistical adjustment for cross-cell contamination. In addition, villages vary in distance to nearest health facility and health facility staffing. Some villages have a dispensary or health center and others are served by facilities outside their boundaries. Other biases could arise if project-provided supplies are differentially accessible to CHA relative to workers based in dispensaries. To address these biases, statistical adjustment will be made for distance to nearest health facility, health facility staffing, and disruption of key supplies at the dispensary level. Finally, an index of health systems strength developed will be included in multivariate models; CHA public health impact may vary according to the strength of the health systems in which CHA are placed.

Based on this information, Connect has developed a counterfactual basis for analyzing project impact on mortality, particularly measures of child mortality, and other measures of impact in comparison and intervention areas. Since Connect is a true experiment, and prior demographic trends are available, rigorous application of hazard regression models is possible. This permits the multilevel modeling of individual prospective longitudinal survival as a function of childhood, familial, community, and programmatic covariates; treatment indicators are adjusted for the population density of CHA exposure, distance-to-service points, and other confounders, such as maternal age and educational attainment, household distance from fixed service points, household relative economic status, and extended family size and composition [48]. The imposition of “time-conditional” models will permit analyses of the survival of all children who have ever been under 60 months of age during the Connect Project period.

Evaluating CHA impact on child mortality relies on the HDSS, a longitudinal data system which collects relational data from households three times annually. Mortality events are registered in conjunction with migration and births, providing a basis for monitoring the risk of childhood death. Conventional procedures for assessing cause of death will permit appraisal of maternal mortality and causes of child mortality [49]. In addition, HDSS modules in the study area have been added to assess proximate determinants of fertility, allowing for detailed analysis of the fertility impact of the CHA.

Hayes and Bennet’s formula published in 1999 for simple sample-size calculation for cluster-randomized trials was used to determine the level of power available to detect the effects of the intervention on health outcomes [50]. Connect embraced Van Breuklen et al’s approach to adjust estimates of statistical power for the loss of efficiency that arises from assigning CHA treatment in clusters, by village [51]. Based on these procedures, we have demonstrated that the study design has 80% power to detect 18% change in under-5 mortality, 20% change in infant mortality, and 25% change in newborn mortality.

Connect will use the detailed registration of demographic information at the individual level to closely monitor changes in intervention and comparison villages. Linked information on individuals, parents, households, or localities provides opportunities to model survival processes as a function of characteristics of their social or economic circumstances. Additionally, a household survey with a sample of approximately 3,300 women of reproductive age was conducted at baseline and will be conducted at endline in the study area to gather additional information on behavioral and care-seeking patterns. These data will permit individual-level analyses, providing a rich picture of relevant health seeking and service utilization trends and pathways at baseline and, by the end of the project, to explain the patterns that underlie survival impact, including patterns associated with care seeking and referral for maternal, newborn, and child emergencies.

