***Community Mobilization and Health Systems Strengthening***	

Mobilization and Outreach	• Convene village groups to identify and discuss priority community health issues • Mobilize community-based responses for emergency referrals and other priority issues

Health Information	• Collect service statistics (CHA) and assist with vital registration at village level • Manage and report community-based service information into broader HMIS

Governance and Leadership	• Attend Village Health Committee, Health Facility Management Team and Health Facility Governing Committee meetings to articulate community health needs and priorities • Support committees in coordinating events and activities as needed

The below table provides an overview of the main tasks CHA are trained and authorized to provide.

Utilizing all of the 101 villages under surveillance in the three districts, villages were randomly assigned to intervention (50) and comparison (51)*.* The number of CHA to serve in each of the intervention villages was determined as one for a population of <1,000; two for a population of 1,000 – 3,999; three for a population of 4,000 – 6,999; and four for a population of >7,000.

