To recruit the CHA, local government solicited and screened applications and then convened a village meeting where qualified applicants were selected through voting. The minimum qualification was completion of a secondary education. Each CHA underwent a nine-month pre-service training in a residential competency-based program after which they were awarded a certificate that allows career progression. The training topics include human biology, community health, clinical skills, reproductive health and family planning, IMCI (including community case management), essential newborn care practices, disease prevention and control, and advocacy and communication. Due to training capacity, CHAs were trained in two cohorts with a total of 57 in the first round and 56 in the second round. All graduates were deployed to their home villages. A third cohort was trained in 2012-13 to increase the minimum number to two CHA per village based on early implementation feedback and to align work assignment according to official government decisions to create hamlets. Although the third round of training did not alter the experimental design, 32 CHA are being added to treatment villages to respond to decisions by the government of Tanzania to create administrative and political functions for hamlets within villages, which necessitates recalibration of CHA work areas according to this new political arrangement. After graduation, CHA are officially contracted and paid as employees of their local government with project funding.

System supports and linkages for the CHA are coordinated by a member of the CHMT. The supervision design is dual: nearby health facility staff provide supervision for technical issues and village governments provide supervision for administrative issues. Health facility supervisors hold a qualification equal or above that of an enrolled nurse. Village governments select a member of the community to serve as the village supervisor based on education level, age, residence in the village, and status in the community. Neither supervisor receives payment for their role as a CHA supervisor. The project provides them with mobile phones, job aids, and bicycles for village supervisors and motorbikes for supervising health facilities.

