#### Evaluation of emergency referral system strengthening

The emergency referral strengthening interventions cover the entire districts and address emergency health conditions among all members of the population, with a focus on pregnant women, newborns, and children under 5. Since only three districts are included in the design, randomization of the referral intervention was not possible and overall assessment of the referral component of Connect is constrained to a pre-post case study. To this end, data extraction from referral forms will be used to assess changes in volume and patterns of emergency referral systems [52,53]. Referral forms will also be used to establish whether changes occurred after introduction of the interventions [54].

Criterion-based audits on emergency-referral cases at baseline and endline will be used to assess changes in quality of management in these cases [55]. Health facility surveys, based on Service Provision Assessments and needs assessments for emergency obstetric care, will be conducted at baseline, midline, and endline for cross-sectional assessment of the relative strength of the health system, particularly as relates to maternal, newborn, and child health and ability to respond to health emergencies. The primary analysis of these data will develop a model that is used to generate measures of facility strength and preparedness for emergencies [56]. This method will provide data for assessing changes related to the provision and utilization of emergency services, particularly for acute maternal, newborn, and child health conditions. The facility survey will also provide data on the health system contextual factors that may affect CHA performance.

The referral system will be monitored in the 101 HDSS communities according to the pace and location of the introduction of CHA support for the referral system. Referral related demographic outcomes — such as maternal and early neonatal deaths in CHA exposed and unexposed communities — will be used to determine if the phasing in of referral has been helped with CHA support relative to having referral logistics without CHA implementation support. Connect will also conduct research using non-mortality referral system outcomes as endpoints. This will test whether the CHA role improves the emergency referral system since indicators will determine whether the referral system works better in villages with CHAs.

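### The child-mortality model adjusts the treatment indicator for CHA density, which is the dose created by randomisation, so the treatment coefficient need not be the effect of placing CHAs in a village

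*Protocol article*

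**What the plan says.** The section on evaluation of the CHA intervention describes multilevel hazard regression for child survival, in which "treatment indicators are adjusted for the population density of CHA exposure, distance-to-service points, and other confounders". The list of confounders continues with maternal age and education, household distance, "household relative economic status, and extended family size and composition".

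The same section plans further adjustments:

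- On comparison-area clients who use CHAs: "This information will permit statistical adjustment for cross-cell contamination".
- On facilities: "statistical adjustment will be made for distance to nearest health facility, health facility staffing, and disruption of key supplies at the dispensary level".
- On system strength: "an index of health systems strength developed will be included in multivariate models".

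The text after Table 2 shows how CHA density arises. Allocation was 50 intervention and 51 comparison villages. "The number of CHA to serve in each of the intervention villages was determined as one for a population of <1,000", rising to four in the largest villages. The training paragraph then reports that "32 CHA are being added to treatment villages", to bring every village to at least two and to fit new hamlet boundaries.

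The article describes no mortality comparison by assigned arm without these terms, and it does not restrict the covariates to baseline values.

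**The concern.** A confounder is associated with treatment and is not produced by it. CHA density is produced by it: assignment creates the density, and a village's density is how much of the intervention it received. The article's question is whether introducing CHAs reduces child mortality. Randomisation answers that through the contrast between assigned villages. Holding density fixed while changing arm asks a different question.

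Observed contamination also arises after randomisation and depends on where CHAs were placed. Supply disruption during the trial is likewise measured after randomisation. Neither belongs in the main estimate without justification.

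The article says that policy approval of a salaried cadre awaits evidence of impact. A treatment coefficient near zero, or too imprecise to read, could be taken as evidence against the cadre when it reflects only how the model was written.

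**Working it through.** **Inputs from the article.** 101 villages (50 and 51); HDSS population 362,307, so a mean of 362,307/101 = 3,587 per village; 14.0% under 5; the CHA staffing bands; 113 CHAs deployed and 32 being added; 80% power for an 18% change in under-5 mortality. Under-5 mortality of 84 to 103 per 1,000 is the national range across the poorest and wealthiest quintiles and serves only as a range.

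**Assumed, because not given.** Two-sided alpha 0.05, between-village coefficient of variation k, length of follow-up, and lognormal village sizes.

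**1. The stated power.** Under-5 person-years per village per year are 0.14 × 362,307 / 101 = 502. The rate is −ln(1−q)/5, or 0.0175 to 0.0217 per year. The Hayes-Bennett formula is

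power = Φ( (r0 − r1)√(c−1) / √[ (r0+r1)/y + k²(r0²+r1²) ] − 1.96 ), with r1 = 0.82 r0 and c − 1 = 49.

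With q = 0.084, y = 2 × 502 and k = 0.25 this gives 79%. Over k = 0.10 to 0.30 and 2 to 4 years it runs from 71% to over 99%. The stated 80% corresponds to k of about 0.24 to 0.31. It is plausible but cannot be reproduced exactly. It describes a two-arm contrast with no density term.

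**2. Density is the dose.** If the intervention villages hold 50/101 of the population (179,360 people), average density is 113/179.36 = 0.63 CHA per 1,000, and 145/179.36 = 0.81 after the additions. Under the staffing rule, density is 2.0 per 1,000 at a population of 1,000, 0.50 at 3,999, 0.75 at 4,000 and 0.43 at 6,999. Within the intervention arm it is a function of village size. No CHAs are based in comparison villages.

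**3. What the coefficient means.** Let T be the arm and D the density (zero where T = 0), with log hazard = a + bT + cD. The average effect of assignment is b + c·m, where m is mean density in intervention villages. The coefficient b is the effect at D = 0, a CHA village without CHAs. If the true effect is β·D/m, then b = 0 and c = β/m, so density absorbs everything.

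**4. Precision.** Ignoring strata and unequal cluster sizes, with 51/101 = 0.505,

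SE ratio ≈ √(1 + 0.505/CV_D²),

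where CV_D is the coefficient of variation of density among intervention villages. CV_D = 0.52 gives 1.7 and CV_D = 0.27 gives 2.8. A wider spread costs less: CV_D = 0.75 gives 1.4.

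**5. Simulation.** Settings: 101 villages, the staffing rule with or without a minimum of two CHAs, average reduction 18%, k = 0.25, 2 years, village-size CV 0.5 to 0.9.

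| Model | Power, constant effect | Effect proportional to density |
|---|---|---|
| Arm only | 73-77% | 49-70% |
| Arm + density, uncentred | 21-37% | coefficient about 0, significant in 5-6% of runs |
| Arm + density centred in the intervention arm | 66-77% | 63-76% |
| Density alone | – | 67-76% |

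In one typical setting, SE(log RR) rises from 0.071 to 0.140. As a check, ln 0.82 = −0.198, so the power is about Φ(0.198/0.071 − 1.96) = 80% against Φ(0.198/0.140 − 1.96) = 29%. The simulated values are 78% and 26%.

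**The case against.** **The model is not called primary.** The article says that the design permits such modelling, never labels it primary or sole, and commits to CONSORT cluster reporting. An unseen analysis plan may contain an assigned-arm contrast. This stands: a reader might infer that the article rules out such an analysis, and it does not. But the density adjustment is a stated choice, not an omission, and the stated reason for it (confounding) is wrong.

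**The power loss depends on parameterisation.** This also stands. A reader might infer that a density term always destroys power. It does not: centring restores 66-77% under a constant effect, and a dose model beats the arm-only model if the effect follows dose. With a constant effect the uncentred coefficient is imprecise rather than biased. The text does not mention centring.

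**The wording may mean scaling treatment by dose.** Possible. The coefficient is then an effect per unit of density, learnt partly from villages of different sizes, and still not the effect of assignment. If exposure includes clients who cross from comparison villages, density there is not exactly zero, but it is then an exposure observed after randomisation.

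**Other covariates.** A reader might infer that facility staffing, family size and the health-systems index are mediators measured after randomisation. The article gives no dates for them as model terms, and a baseline facility survey exists: facility surveys "will be conducted at baseline, midline, and endline for cross-sectional assessment of the relative strength of the health system". Nothing shows that assignment changes staffing or dispensary stock; Table 4 attributes stock-outs to national supply problems. A reader might also hold that the index must enter as an interaction, but including it in the models does not exclude one. Distance, maternal age and education are harmless.

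**Conclusion.** The point holds for CHA density and, more modestly, for observed contamination and supply disruption during the trial. As written, the mortality model treats the dose of the randomised intervention as a confounder, and on neither plain reading is the treatment coefficient the effect of assigning CHAs to a village.

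Under the uncentred reading, the standard error grows about 1.7 to 2.8 times and power falls from about 75% to 21-37% with a constant effect. With a dose-proportional effect, a true average 18% reduction shows as a coefficient of about zero. These sizes rest on the assumed k, follow-up and village-size spread, and on density entering uncentred. The algebra in step 3 does not depend on the first three. For contamination and supply disruption no size was computed, and the documents do not show that assignment alters dispensary supply. The objection there is only that they are observed after randomisation.

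**What to change.** State that the main child-mortality estimate is the contrast by assigned village, adjusted for the four population-size strata and baseline covariates only. Baseline values of distance to facility, facility staffing and the health-systems index can stay, with the covariate dates given.

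Move CHA density, observed contamination and supply disruption during the trial to secondary dose or mechanism analyses. Where arm and density appear together, say how density is coded (for example, centred among intervention villages) and what the arm coefficient then means.

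The cost is wording: the data are already planned and the adjusted models remain as secondary analyses. There is one small statistical price. If the effect truly follows dose, the assigned-arm contrast is somewhat less powerful than a dose model (49-70% against 67-76% in the simulation), and the dose model stays available as a secondary analysis.
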